### Randomization and blinding assignment of interventions

Using computer-generated random numbers, an allocation sequence for the recruited nursing homes (clusters) has been generated that complies with the statistical power calculations and the requirements of participating nursing homes. In each block, two homes has been randomly assigned. The random-sequence document is available neither to the enrolled nursing homes nor the participating older adults. In order to conceal the sequence, each nursing home was simply informed just one month prior to each home starting to recruit residents and get consent forms. None of the participating homes know the allocation sequences of either itself or others. A data manager independently has allocated the sequence and passed the results to the SPEC consultant enrolling the participating nursing homes. Outcome assessors and data analysts will be blinded after assignment to interventions. Outcome assessors will not be aware of the on-going intervention study. They will be responsible for data collection and entry in the electronic form. Data analysts will get the data without any identification information on the participating institutions and individuals. Blinding is not possible for trial participants and care providers in this study because it uses a stepped-wedge design where all participants receive interventions sequentially. Older residents will be informed they will receive an intervention upon consent, while outcome assessors and data analysts will be blinded until the end of the study.

### Data collections, management, and monitoring

Data collection will be conducted as outlined in Tables 2 and 3. Primary and secondary outcome data are being collected by trained external assessors who are also nurses with clinical knowledge about and experience with caring for older adults using the cloud-based SPEC system. For the external assessors, a one-day intense education program and a follow-up are offered: the program begins with an overview of the study, measurement plan, and responsibilities of the assessors. Then the instructors, who have extensive knowledge of measures and field data collection experience, provide an item-by-item, standardized, manual-based review of the study instruments, followed by a Q&A and discussion session with example scenarios. The later part of the education program consists of how to use the web-based data collection and storage program along with mobile data collection tools such as an iPad and/or cell phone. Along with a lecture session, a demonstration and practice session is provided using educational materials including detailed instructions and exercises. In order to become familiar with the cloud-based SPEC system, trainees are asked to do data entry and storage for several mock-cases, entering them into the system independently within a few weeks after the training session. To increase the reliability of assessment, double-assessment on a few random cases is also done by a pair consisting of an experienced assessor and a new assessor. On-going support for data collection will be provided via KakaoTalk, phone call and face-to-face meeting throughout the entire data collection process; and a helpdesk for the technical issues related to the use of the SPEC system is also provided.

Data of staff-level outcomes before and after the program implementation will be collected from nursing-home care staff members who are involved the SPEC program. Using double-blind methods, the staff members cannot be identified by the research team, which is a way to prevent bias in responses. Technology/innovation acceptance of care staff members will be measured using a survey instrument about one month from the first use of the SPEC system and then re-evaluated at the end of the intervention to compare the difference in the staff’s perceptions of technology use. A process evaluation will be conducted before, in the middle, and after each SPEC component is implemented. Qualitative interviews with the onsite SPEC coordinators in each home along with quantitative data on intervention fidelity will be collected.

To promote participant retention and complete follow-up, the SPEC consultant checks with the onsite SPEC coordinators regularly on the status of the intervention implementation in each site. Also, they are asked to report any issues with the participation status of older residents (e.g., transfer to hospital, death, etc.). If any discontinuation of participation occurs, a short-form discharge/discontinuation report is filled out immediately by the onsite SPEC coordinators, the nurse-social worker pair. Using the reports, the reasons for and patterns of discontinuation are monitored, and strategies to prevent such events are discussed in the weekly research team meeting.

### Data analysis plan

#### Effect evaluation

Baseline differences between clusters during the first control period will be tested using chi-square tests and ANOVA. The primary analysis will be the evaluation of the interventional effect of the SPEC program in nursing homes. The intervention effect on the primary outcome and secondary outcomes described above will be estimated using a multilevel regression analysis to account for the clustered structure [54]. We will use a generalized linear mixed effects model [54], which allows inclusion of both fixed (intervention, time) and random factors. In particular, two random effects will be introduced, one at the cluster (nursing home) level and the other at the individual (resident) level. The test statistic to assess any significant benefit of the intervention will be calculated. We will use two-sided p-values with alpha = 0.05 for level of significance. Compliance issues will be handled as in Jo et al. [55].

A secondary analysis will be conducted to adjust for the potential confounding effects of pre-randomization variables. The same generalized linear mixed effects model will be used to model the primary and secondary outcomes, adjusted for socio-demographic variables including age, sex, physical status, and cognitive status as well as an intervention indicator and time. We will also investigate the effect of the duration of the intervention by adding an interaction term between time and intervention as a fixed effect. Furthermore, subgroup analysis will be used to explore the subgroup-specific effects of the intervention on outcomes. The interaction effects of the intervention with dependency in activities of daily living and cognitive impairment will also be explored. When a statistically significant difference is found, the study population will be split to examine the results for each subgroup separately. We will also conduct an analysis of the intervention effects on facility-level pre-post measurements using a t-test. In addition, we will develop models to evaluate the impact of the program on resident-level outcomes while adjusting for facility-level factors. A *p*-value of 0.05 or less will be considered to be significant.

We will first conduct an effect analysis based on the intention-to-treat (ITT) principle [56], in which all older residents in the SPEC program will be included. Imputation methods will be implemented to handle missing data to enable ITT analysis [57]. We will allow new individuals to participate in the program at every time period; sensitivity analyses to assess the effect of attrition and inclusion of residents will also be conducted. The data monitoring committee (DMC) is composed of the PI, data managers, and statisticians; the committee is responsible for the data quality across the whole data-collection, analysis, and reporting process. The DMC is independent of the research-funding agency and has no competing interests.

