### Outcomes

Quality of care is the primary outcome, and several secondary outcomes including quality of life will be measured. We have also included process measures and staff-/organization-related measures as complementary. All outcomes and their measurement plans are summarized in Table 2, except the process evaluation measures, which are in Table 3.

**Table 2 Tab2:** Overview of the outcome variables, measures, and observation points

Variable	Data Source/Instrument	Measurement Points	Unit of Analysis
Primary Outcomes			
Quality of Care	interRAI LTCF quality measures (composite score)	T0 (baseline), T1, T2, T3	Resident
Secondary Outcomes: Patient-Related			
Quality of Care	interRAI LTCF quality measures (individual score)	T0 (baseline), T1, T2, T3	Resident
Care Needs	Number of triggered clinical action points of interRAI LTCF	T0 (baseline), T1, T2, T3	Resident
Functional Health	Bathel index; Mini-Mental Status Examination; Patient Health Questionnaire	T0 (baseline), T1, T2, T3	Resident
Quality of Life	EuroQol(EQ)-5; interRAI HRQoL; interRAI self-reported QoL (SQoL)	T0 (baseline), T1, T2, T3; T1 & T3 (SQoL)	Resident
Patient Satisfaction	Client Satisfaction Questionnaire	T1 & T3	Resident
Health Care Utilization	Hospital admissions; emergency department visits	Every three months	Resident
Costs	Questionnaire on the cost; direct and indirect costs	Every three months	Resident
Other Outcomes: Care Staff/Organization-Related			
Empowerment	Psychological Empowerment Instrument	T1 & T3	Nursing Home
Communication Satisfaction	Communication Satisfaction Questionnaire	T1 & T3	Nursing Home
Organizational Commitment	Organizational Commitment Questionnaire	T1 & T3	Nursing Home
Job Satisfaction	Job Satisfaction Scale	T1 & T3	Nursing Home
Technology/Innovation Acceptance	Modified Technology Acceptance Model Questionnaire	T1 + 1 month & T3	Nursing Home

**Table 3 Tab3:** Process evaluation on intervention and implementation strategies

Topic	Data Source/Analysis	Measurement Points	Unit of Analysis
Recruitment of cluster	[Qualitative analysis] - Measurement from documentation of recruitment & allocation process by research team	During recruitment of clusters	Nursing home

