#### Primary outcome measure

The primary outcome measure of the study is *quality of care* (*QoC*)*,* measured by a composite score of quality indicators (QIs) in the interRAI LTCF, which has good psychometric properties [23], similar to the primary outcome measures of the MIC intervention in resident care facilities in the Netherlands [14] and the European Services and Health for Elderly in Long-TERm Care (SHELTER) study [24]. The outcomes will be measured four times: at T0 (baseline), T1 (3 months; the end of observation period), T2 (6 months; 3 months after the beginning of the intervention), and T3 (9 months; the end of the intervention, 6 months after its start). Resident outcome data will basically be collected every three months by external nurse assessors trained by the SPEC research team.

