#### Secondary outcome measures

*QoC*, measured by individual interRAI QIs, is a secondary outcome measure to observe the effects of the SPEC intervention on quality in various health and function domains separately, assuming the impact of the program may not be the same across the domains.

*The extent of care needs* is measured with the number of total triggered CAPs in four categories: functional performance, cognition/mental health, social life, and clinical issues [19]. We will examine the change in the number before and after the program implementation. Some CAPs may have too low a prevalence in Korean nursing homes, which would threaten their validity, so we will remove them from the final set of CAPs for the analysis.

*Functional health* will be measured by three measures (the Modified Bathel index, Mini-Mental Status Examination, Patient Health Questionnaire). The Bathel index is used to measure performance of physical functions in activities of daily living. We will adopt the modified version by Shah et al. [25], which has demonstrated high inter-rater reliability (0.95) and test–retest reliability (0.89) as well as high correlations (0.74–0.8) with other measures of physical disability [26]. The Mini-Mental Status Examination (MMSE) [27] is used to measure cognitive impairment using a 30-point questionnaire. The Korean version of MMSE (K-MMSE) has good sensitivity (0.70-0.83) and convergent validity (0.78) [28]. The PHQ-9 is a depression module of the PHQ (Patient Health Questionnaire) developed by Spitzer et al. [29] and translated into Korean by Han et al. [30]. The Korean version of the PHQ-9 has good internal consistency (0.88) and convergent validity (0.74).

The *quality of life* (QoL) of older nursing home residents will be measured with the Korean version of the EQ-5D-5 L. The EQ-5D, developed by EuroQol Group, is a measure of health-related QoL that has five items, and each item measures different dimensions of health–-mobility, self-care, usual activities, pain/discomfort, and anxiety/depression [31]. The EQ-5D-5 L will be adopted because 5 L is known for having better sensitivity and a lower ceiling effect than other versions of EQ-5D in Korea [32]. General QoL of residents will be measured with the interRAI Self-Reported QoL (interRAI SQoL) [33].

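### The pre-post t-test on the four facility-level staff scales credits a steady secular trend to SPEC and leaves the stepped-wedge comparison unused

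*Protocol article*

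**What the plan says.** The Effect evaluation section gives two different analyses to two groups of outcomes. For the first group, "The intervention effect on the primary outcome and secondary outcomes described above will be estimated using a multilevel regression analysis". That model is a generalized linear mixed model, "which allows inclusion of both fixed (intervention, time) and random factors", so it adjusts for time. For the second group the section says "We will also conduct an analysis of the intervention effects on facility-level pre-post measurements using a t-test". It mentions neither a time term nor a comparison between homes for that test, and it takes p-values of 0.05 or less as significant.

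Table 2 shows which outcomes fall in the second group. Under "Other Outcomes: Care Staff/Organization-Related", separate from the secondary outcomes, it lists empowerment, communication satisfaction, organizational commitment and job satisfaction. Each is measured at T1 and T3, with the nursing home as unit of analysis. Technology acceptance is in the same block but is measured at T1 plus one month and at T3.

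The Primary outcome measure section defines "T1 (3 months; the end of observation period") and places T3 at nine months, six months after the intervention starts. Under Study design, two homes start every three months over five steps, and the study lasts about 21 months.

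**The concern.** The test is described as an analysis of intervention effects, but it compares each home only with its own past. Anything that moves staff scores steadily over the calendar, such as changes in staffing, pay or the sector's attention to quality, is counted as an effect of SPEC. The Discussion offers estimation from both between- and within-cluster comparisons as a reason for choosing a stepped-wedge design. For these four scales the between-home half of that is set aside, although the planned data contain it. At stake is whether a significant change on a staff scale may be reported as an effect shown by a randomized trial or only as an uncontrolled before-after difference.

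**Working it through.** **Is there a figure to reproduce?** No. The article gives no power, variance or effect size for the facility-level test. The sizes below rest on stated assumptions.

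**1. Calendar.** Five sequences of two homes start three months apart. T1 falls at months 3, 6, 9, 12 and 15, and T3 at months 9, 12, 15, 18 and 21. The last T3 agrees with the stated 21 months. At months 9, 12 and 15, two homes are at T3 while two others are at T1. These are concurrent controls.

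**2. Bias.** Let scores drift by b per quarter in all homes. In every home, expected T3 minus T1 = effect + 2b. Averaging over homes does not change this. A lasting one-off shift behaves differently: it enters only for sequences whose T1 precedes it and whose T3 follows it. A shift between months 9 and 12 affects sequences 2 and 3 only, so 2/5 of it enters. Between months 3 and 6 it affects sequence 1 only, so 1/5 enters.

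**3. False-positive rate.** Assumptions: 20 staff per home, total SD 1, intracluster correlation 0.05, and a t-test paired on 10 home means (9 df, critical value 2.262). With cluster autocorrelation c, the variance of a home's change is 2 × [0.05(1 − c) + 0.95/20].

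| c | Variance of change | SE of mean change | Rejection, b = 0.05 | Rejection, b = 0.10 |
|---|---|---|---|---|
| 1 | 2 × 0.0475 = 0.095 | √(0.095/10) = 0.097 | 15% | 45% |
| 0.5 | 2 × 0.0725 = 0.145 | √(0.145/10) = 0.120 | 12% | 32% |

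The rates come from the noncentral t distribution with noncentrality 2b/SE. For c = 1 this is 0.10/0.097 = 1.03 and 0.20/0.097 = 2.05. The nominal rate is 5%.

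Without assuming staff numbers or correlations, the same test rejects 11%, 29%, 56% and 80% of the time when the six-month drift is 0.25, 0.5, 0.75 and 1.0 SD of the home-level change.

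**4. Can the planned data separate trend from effect?** Yes, with a random home effect. Take linear time and c = 1, write r for the intracluster correlation and w = (1 − r)/20.

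- The mean within-home change estimates effect + 2b, with variance 2w/10 = 0.2w.
- The slope of the home averages across the five sequences estimates b. The sum of squares of sequence number is 2 × (4 + 1 + 0 + 1 + 4) = 20, so its variance is (r + w/2)/20.
- The adjusted effect is the first minus twice the second. Its variance is 0.2w + 4(r + w/2)/20 = 0.3w + 0.2r.

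| r | SE, pre-post: √(0.2w) | SE, adjusted: √(0.3w + 0.2r) | Ratio |
|---|---|---|---|
| 0.01 | 0.099 | 0.130 | 1.3 |
| 0.05 | 0.097 | 0.156 | 1.6 |
| 0.10 | 0.095 | 0.183 | 1.9 |
| 0.20 | 0.089 | 0.228 | 2.55 |

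With categorical quarters, generalized least squares gives 0.163 at r = 0.05 and a ratio of 2.6 at r = 0.20. The second bullet shows that the trend is learned from differences between homes. With home fixed effects, T1 and T3 alone do not identify the intervention effect.

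**5. Technology acceptance.** It is first measured "about one month from the first use of the SPEC system and then re-evaluated at the end of the intervention". Both measurements follow the start of the intervention, so no analysis of them can give an intervention effect.

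**The case against.** The scope is narrow. The article calls the staff and organization measures complementary, and the resident outcomes have a time-adjusted model. No conclusion on quality of care or quality of life depends on this test. That stands, and it limits the weight of the point.

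The adjusted analysis is also less precise and rests on a random-effect assumption in 10 homes. Nor does it remove everything: each T1 is the first staff survey and each T3 the second, so any effect of answering twice stays confounded with SPEC whatever calendar adjustment is made. Both stand. They argue for modest claims, not for treating a before-after change as an intervention effect.

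The size of any trend is unknown. The government inspection in the Discussion is named as a threat to homes' commitment, not as a trend in staff scores. That stands too: the rejection rates are conditional on a trend, while the 2b bias follows from the design.

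Three stronger readings are tempting but not supported:

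- A reader might infer that the count of triggered clinical action points has the same defect, since the article says "We will examine the change in the number before and after the program implementation". Table 2 lists it as a secondary resident outcome at T0 to T3, and the Effect evaluation section puts secondary outcomes in the mixed model.
- A reader might infer from "the staff members cannot be identified by the research team" that the t-test must be unpaired on individual staff and so ignores the home. The plan says facility-level and Table 2 sets the home as unit. Anonymity does not prevent pairing home means.
- A reader might infer that any calendar influence passes through in full. Only a steady trend does; a one-off shift is diluted by the staggered starts.

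**Conclusion.** The point holds for the four staff scales measured at T1 and T3. The planned test cannot tell a SPEC effect from a steady trend, and its bias is twice the quarterly trend. Under the assumptions above, with cluster autocorrelation from 0.5 to 1, the false-positive rate is about 12–15% for a trend of 0.05 SD per quarter and 32–45% for 0.10 SD. With no trend the test keeps its nominal level. Technology acceptance supports no effect estimate under any analysis.

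That the t-test applies to these scales is an inference, but a firm one: Table 2 gives them the nursing home as unit and pre and post time points, and the mixed model is stated only for primary and secondary outcomes. The change should be made, but it does not touch the trial's main conclusions.

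**What to change.** Estimate the intervention effect on empowerment, communication satisfaction, organizational commitment and job satisfaction with a mixed model: random home effect, fixed effects for intervention and calendar time (linear if the quarters are too sparse), and small-sample degrees of freedom. This brings in the homes at T1 while others are at T3, at months 9, 12 and 15. Keep the t-test if wanted, but label it as descriptive before-after change. Report technology acceptance descriptively only. State that the adjusted estimate relies on between-home contrasts and the random-effect assumption in 10 homes, and that survey order cannot be separated from the intervention.

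No new data are needed, and the Trial status section says analysis had not started. The price is precision: the standard error is about 1.3 times that of the pre-post difference at an intracluster correlation of 0.01, 1.6 times at 0.05, 1.9 times at 0.10 and 2.6 times at 0.20.

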### Objectives

The aim of the study is to evaluate the effectiveness of a technology-enhanced, multidisciplinary, integrated care management model named Systems for Person-centered Elder Care (SPEC). The primary research question is whether the SPEC model (intervention program), a theory-driven, technology-enhanced, integrated care model, is effective for improving quality of care, compared to care reflecting the current practice pattern in nursing homes in South Korea. We hypothesize a person-centered, integrated, multidisciplinary care model will improve the quality of nursing care, which will in turn promote the quality of life of older residents. To evaluate the proposed model, we will conduct a clustered randomized control trial (RCT) for older adults residing in nursing homes, and the model will be implemented at the nursing home (cluster) level. We will also conduct economic and process evaluations.

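### One two-sided 0.05 rule covers the primary composite and every resident-level secondary outcome, with no order, adjustment or exploratory label for the secondaries

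*Protocol article*

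**What the plan says.** The scope of the analysis is set in the protocol article under Effect evaluation: "The intervention effect on the primary outcome and secondary outcomes described above will be estimated using a multilevel regression analysis". The same paragraph fixes the level: "We will use two-sided p-values with alpha = 0.05 for level of significance". The next paragraph adds a covariate-adjusted repeat ("The same generalized linear mixed effects model will be used to model the primary and secondary outcomes") and ends with "A *p*-value of 0.05 or less will be considered to be significant".

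Table 2 ranks outcomes as primary (the composite quality-of-care score), secondary (resident-related) and other (staff and organisation). The secondary block holds the individual quality indicators, the count of triggered care-need protocols, three functional scales, three quality-of-life scales, satisfaction, hospital admissions, emergency visits and costs. Under Secondary outcome measures, the individual indicators are included "to observe the effects of the SPEC intervention on quality in various health and function domains separately". Their number is not stated.

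Softer labels appear elsewhere. Staff and process measures are called complementary, and subgroup and interaction analyses are described as exploring. No such label is given to the resident-level secondaries.

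**The concern.** The article ranks its outcomes but attaches no inferential consequence to the rank: a secondary result with p at or below 0.05 is called significant on the same terms as the primary result. If the composite showed nothing, the rule as written would still let the report name a significant improvement in some care domain, some functional or quality-of-life scale, or some utilisation measure. With this many separate looks, one such result is quite likely by chance alone. The exposure is greatest for the individual indicators, because they are meant to be read one domain at a time and there may be many of them.

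**Working it through.** **1. The plan's own figure.** Under Sample size & recruitment, the whole 0.05 goes to the composite. The inputs are proportions 0.115 and 0.182 (difference 0.067), cluster correlation 0.01, resident correlation 0.25, 10 homes in five sequences of two, and four measurements per home (two control, two intervention) over 8 calendar points. With σ² = 0.115 × 0.885 = 0.1018, I is the identity matrix and J the all-ones matrix. The covariance of a home's four means is

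V = 0.01σ²J + (0.25σ²J + 0.74σ²I)/n,

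and power = Φ(0.067/√var − 1.96), where var is the generalised-least-squares variance of the intervention effect with fixed time effects. The smallest n with at least 80% power is 33 (80.8%), which matches the article's figure for an outcome measured separately at each time point. The figure of 45 cannot be fully rebuilt because its correlation matrix is not given. The bed count follows: 45/(0.8 × 0.85) = 66.2, so 67. The primary test is thus sized at two-sided 0.05, and that error rate is not in question.

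**2. Counting the secondaries (Table 2).** Care needs 1, functional scales 3, quality-of-life scales 3, satisfaction 1, utilisation 2, costs 1: total 11 without the individual indicators. Costs are counted once, although Economic evaluation also uses them in an incremental cost-effectiveness ratio. The adjusted repeat analyses are not counted.

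**3. Chance of at least one false result.** Assume no true effect on any of k outcomes. With independent tests:

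- either direction: 1 − 0.95^k; for k = 11, 1 − 0.95^11 = 0.431
- benefit only (0.025 per test): 1 − 0.975^k; for k = 11, 1 − 0.975^11 = 0.243

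For correlated tests, let Z_j = √ρ·U + √(1−ρ)·E_j with U and E_j standard normal. Count how often any |Z_j| exceeds 1.96 (either direction) or any Z_j exceeds 1.96 (benefit). This used 400,000 simulated sets. The documents give neither the correlations nor the number of indicators, so both are assumptions; k = 31 assumes 20 indicators.

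| Tests | Direction | ρ = 0 | ρ = 0.5 | ρ = 0.8 |
|---|---|---|---|---|
| 11 (no indicators) | either | 43% | 30% | 18% |
| 11 (no indicators) | benefit | 24% | 15% | 9% |
| 31 (20 indicators assumed) | either | 80% | 51% | 26% |
| 31 (20 indicators assumed) | benefit | 54% | 26% | 13% |

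The reference is 5% per test for the either-direction rows and 2.5% for the benefit rows. Even the mildest case (11 tests, ρ = 0.8) gives 18/5 = 3.6 times and 9/2.5 = 3.6 times the per-test rate.

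**The case against.** The strongest objection is that a condensed article commonly leaves multiplicity for secondaries to the full protocol or the analysis plan, so its absence here is no error. That would settle the matter if the article were silent. It is not: it states a threshold and what passing it means, for primary and secondary outcomes alike. An analysis plan that ordered or downgraded the secondaries would have to override this text. The closing sentence could be read as covering only the adjusted, subgroup and facility-level analyses of its own paragraph, but the earlier 0.05 sentence already covers both outcome classes.

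Other points stand and limit the concern. Outcomes are ranked, one research question is named as primary, and the trial is powered on the composite alone, so what is missing is a consequence of the rank and a rule among the secondaries. The wording on the individual indicators is partly descriptive.

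Two stronger readings are tempting, and the documents do not support them:

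- **Quality of life.** The Objectives say that better care is expected to lead to a further gain ("which will in turn promote the quality of life of older residents"), and three scales could each show it. A reader might infer that a false quality-of-life benefit is far more likely than 5%. For three tests the benefit-only chance is 7.3%, 6.3% or 4.9% at correlations 0, 0.5 and 0.8. That exceeds 2.5% per test but is not far above 5%. The text also leads with EQ-5D-5L, which feeds the QALYs; interRAI HRQoL appears only in Table 2.
- **Subgroups.** The article plans: "When a statistically significant difference is found, the study population will be split to examine the results for each subgroup separately". A reader might infer that this multiplies false subgroup claims. After a falsely significant interaction, at least one of two equal subgroups has p < 0.05 in about 65% of cases, but the false interaction itself has probability 5%. The joint chance is 0.05 × 0.65 = 3.25% per two-group factor, against 1 − 0.95² = 9.75% if both subgroups were tested without that condition. The condition therefore restrains false claims, in analyses already described as exploring.

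**Conclusion.** The point holds for the labelling of the secondaries and for the set of individual indicators. The article calls any secondary p-value of 0.05 or less significant, without order, adjustment or an exploratory label. With no true effects, the chance of at least one such result among the 11 countable secondaries is 18% to 43% in either direction, and 9% to 24% for a false benefit. The indicators raise this by an amount that cannot be fixed, because their number is not given. The figures rest on equal correlations of 0 to 0.8, tests that hold their nominal level, and no true effect on any counted outcome.

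The primary test keeps its 5% error, so a reader should not infer that the main conclusion is compromised. This is a worthwhile correction of moderate weight.

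**What to change.** Replace the closing significance sentence under Effect evaluation, and align the earlier 0.05 sentence with it, so that the text states:

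1. The conclusion on effectiveness rests only on the intervention effect on the composite, tested at two-sided 0.05.
2. Secondary outcomes are supportive or exploratory and are reported as estimates with 95% confidence intervals.
3. If the individual quality indicators are tested, Holm or false-discovery-rate control is applied within that set, and their number is stated.

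Naming one quality-of-life scale as key secondary, for example EQ-5D-5L, is optional; other arrangements would also do.

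The cost is wording only. Trial status reports that data analysis has not started, so the rule can be set before results are seen. No new data are needed and the power of the primary test is unchanged. The small downside is that an isolated secondary p-value below 0.05 can no longer be claimed as a significant effect.
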